#### Patient safety

We are convinced that the use of the Canadian C-Spine Rule is accurate and reliable, and that the proposed study will respect patient safety at all times. Use of the rule will be encouraged, but the decision to order radiography will always be at the discretion of the attending physician, as it is at present. Physicians will know that they can "override" the rule at any time when they have concerns about patient welfare. The Canadian C-Spine Rule has proven to be very sensitive in identifying CSI and, in fact, one could argue that the rule is more accurate than Canadian emergency physicians. We do know that, in current Canadian practice without the rule, patients are being discharged from the ED with undiagnosed fractures. We expect this occurrence to be less frequent in the proposed study when the rule is available as a guide.

### Ethical considerations

All the respective research ethics boards have approved the study without the need for informed patient consent at the time of the ED visit. During a particular period in time at a given site, all eligible patients will be managed by the physicians in the same manner, because the unit of study allocation is the hospital, not the patient. As is typical of cluster allocated, matched-pair design studies, individual patients will not be randomized and physicians will order cervical spine radiography in a similar fashion for all patients at their site [48]. Patients will not be subjected to new therapy, invasive procedures, undue risk or discomfort, or use of diagnostic radiography beyond that which would normally be required in the course of patient care. Physicians will be encouraged to use the Canadian C-Spine Rule as a guide for ordering radiography, but will ultimately base their decision on their own judgment as to what is the safest way to manage each individual patient. We note that Canadian physicians are already selective in ordering C-spine radiography, and omitted radiography for 28.3% of cases in phase II. At the same time, we know that the physicians missed some fractures. Patient confidentiality will be maintained throughout the study, and patient names will be removed from all records. The small numbers of patients who are selected for follow-up telephone interviews will have an opportunity to give verbal consent to the ED registered nurse who makes the call. This is consistent with the approach approved by the research ethics boards for follow-up in phases I and II. The safety of the study will be overseen by an independent data monitoring safety board, comprised of a biostatistician, an emergency physician, and a neurosurgeon. This board will have the mandate to terminate the study at any time should there be concerns about adverse patient outcomes.

### Setting

The study setting will be six "teaching" and six large "community" hospital EDs, with a combined annual ED volume of approximately 670,000 patient visits. We believe that the generalizability of our findings will be greatly enhanced by including both teaching and community hospitals from a variety of cities (population range 30,000 to 4,000,000) in different areas of Canada. We define a "teaching" hospital as one that is a core educational institution for a medical school's undergraduate and postgraduate students, and whose hospital staff physicians have full-time appointments to that medical school. "Community" hospitals may provide experience for some medical trainees, but the majority of patient care is provided by staff physicians who do not have fulltime appointments with a medical school.

### Study interventions

#### Control sites

No specific interventions will be undertaken to alter the cervical spine radiography ordering behavior of the ED physicians. These sites will exemplify the impact of "diffusion" of new medical information. The Canadian C-Spine Rule will be familiar to some clinicians because of the publication of our phase I results in *JAMA *in October 2001, as well as scientific presentations at national meetings in Canada and the U.S. and a few presentations at continuing education meetings in Canada.

#### Intervention sites

We intend to pursue simple and inexpensive strategies to actively implement the use of the Canadian C-Spine Rule at the intervention sites. Therefore, we have designed an intervention that we consider is deliverable throughout Canadian settings with few additional resources.

#### Details of planned interventions

Each ED physician group will be asked to discuss and agree to a policy of ordering cervical spine radiography for alert and stable trauma patients according to the Canadian C-Spine Rule. Minor educational initiatives for the ED physicians will include the distribution of manuscripts, pocket cards, and posters, as well as a single one-hour teaching session to review the evidence and clinical application of the Canadian C-Spine Rule. The ED and Radiology departments will collaborate to institute a process-of-care modification with a mandatory "online" reminder of the Canadian C-Spine Rule at the point of requisition for cervical spine radiography. All cervical spine radiography ordered in the ED will require that the ordering physician complete a special paper or computer-based requisition that includes the Canadian C-Spine Rule algorithm criteria. The physician must "check off" the criteria, or the radiology department will not process the request. The physician may override the rule, and order radiography according to his/her clinical judgment, but will be asked to indicate the reason. Those sites that use paper requisitions will implement a new pad of special cervical spine radiography requisitions. Those sites that order radiography by computer will have an on-screen version of the rule made available by software modification.

#### Rationale for choice of intervention

We have designed our intervention based upon theoretical considerations, currently available evidence, and discussions with collaborators. The theory of planned behavior proposes that behavior is determined by the individual's intentions to engage in a behavior, and the degree of control they feel they have over that behavior. Intention strength is determined by three variables: attitudes toward the behavior, subjective norms, and perceived behavioral control [49]. ED physicians' intentions to use the Canadian C-Spine Rule would be weak if they were not convinced that the rule would reduce unnecessary x-rays, or if they thought that it was unimportant to reduce unnecessary x-rays (attitudes to the behavior), if they believed that important colleagues did not think that it was important to follow the C-spine rules (subjective norms), or if they did not think that it was possible to follow the rules (perceived behavioral controls). It is recognized increasingly that other factors (i.e., problems of information processing in busy clinical surroundings) intervene between intentions and behaviors that could result in failure to follow the C-spine rules, even if the physician intends to do so [50]. Our interventions will target these different barriers. The educational interventions will target physicians' attitudes toward the C-spine rules. The local consensus process will target physicians' subjective norms by getting buy-in from all the local key stakeholders. The mandatory online reminder will prompt physicians to follow the rule, if they are considering radiography in alert and stable trauma patients.

Empirical evidence for our choice of intervention is available from the review by Solomon and colleagues [34]. They suggest that local consensus processes predisposes to behavior change, especially if coupled with system changes. They also note that the combinations of educational and system changes are more likely to lead to improvements in test ordering. Grimshaw and colleagues conclude that "Reminders are the intervention that have been evaluated most ... [and]...are a potentially effective intervention ... likely to result in moderate improvements in process of care". Further, the use of obligatory reminders appears more successful than voluntary reminders [51]. In discussion with our collaborators, these interventions appeared to be achievable and had face validity.

### Outcome measures and data collection

#### Measures of clinical impact

The following will be collected at both the intervention and control sites during all three study periods by dedicated study personnel who will review daily patient logs, ED patient records, radiology reports, and inpatient records.

Cervical spine radiography ordering proportions will be the primary study outcome, such as the proportion of eligible blunt trauma patients referred for plain cervical spine radiography during the initial ED visit. Daily patient census logs will be reviewed to identify potential injury patients, and then ED patient records (e.g., ambulance call reports, nursing notes, and physician notes) will be assessed to determine eligibility. Radiology reports and census lists will be used to determine if cervical spine radiography was performed.

*Number of missed CSI, such as number of clinically important CSI not identified during initial ED visit*. We validated the safety of the Canadian C-Spine Rule with detailed follow-up of patients in phase II. In order to significantly reduce the resources required for phase III, we propose not to specifically follow all patients who do not undergo radiography in the ED. Telephone follow-up of patients is very labor intensive and expensive. Rather, we propose to institute a strategy of surveillance to identify the uncommon occurrence of a fracture missed because no radiography was ordered. The more common missed fracture cases due to mis-reading of the radiograph will be identified through the normal radiology department quality assurance processes. ED patient visit logs at each study site will be monitored for 30 days to identify return visits by patients who do not undergo radiography during their ED visit. In addition, we will review the neurosurgery patient logs at all neurosurgical centers that are the traditional referral sites for the study hospitals. In many cases, the regional neurosurgical centers will be our study hospitals. Application of the same surveillance approach, regardless of phase or intervention group, minimizes the likelihood of bias. We recognize that there is a very small risk of not identifying a missed fracture, but feel that this approach is pragmatic and feasible.

*Number of serious adverse outcomes, such as development of neurological deficit after initial assessment in ED*. We will use the same surveillance approach described above for identifying missed fractures to identify the extremely rare occurrence of motor weakness and disability that develops after initial assessment in the ED.

*Length of stay in ED, such as the total length of stay from registration to discharge for patients who are neither admitted nor have a CSI*. This will be considerably impacted by the duration of cervical spine immobilization and radiography procedures.

Patient satisfaction with ED care will be determined by a random sample of 5% of "before" and "after" period patients (both those who did and those who did not receive radiography), who will be asked via telephone interview to rate their satisfaction on a five-point Likert scale at 30 days.

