#### Summary of methods

This prospective cohort study was conducted in the emergency departments of nine Canadian tertiary care hospitals. The Canadian C-Spine Rule and NEXUS criteria were interpreted by 394 physicians for patients before radiography. A second physician independently assessed some patients for the same criteria when feasible, and inter-observer agreement was determined. The primary outcome, clinically important CSI, was evaluated after the clinical assessment by standard plain radiography of the cervical spine, optional flexion-extension views, and CT, if clinically indicated.

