#### Specific objectives

The goal of phase III is to evaluate the effectiveness and safety of an active strategy to implement the Canadian C-Spine Rule into physician practice in multiple EDs, compared to a control strategy that relies upon passive measures. Specific objectives are to:

*Determine clinical impact *by comparing the intervention and control sites, individually and collectively, during the "before" and "after" periods for:

a) Cervical spine radiography rates, such as proportion of potential injury patients referred for radiography; this is the primary study objective;

b) Number of missed CSI, such as clinically important CSI not identified during initial ED visit;

c) Number of serious adverse outcomes, such as development of neurological deficit after initial assessment in ED;

d) Length of stay in the ED, such as the time from arrival until discharge; and

e) Patient satisfaction with ED care, particularly when cervical spine radiography is not ordered.

*Determine sustainability *of clinical impact by comparing the intervention and control sites, individually and collectively, during the "after" and "decay" periods for objectives a)-d) above.

*Evaluate performance *of the Canadian C-Spine Rule, during the "after" period at the intervention sites:

a) Accuracy of the rule, such as sensitivity and specificity for identifying clinically important CSI;

b) Physician accuracy in interpretation of the rule; and

c) Physician comfort and compliance with use.

*Conduct an economic evaluation *to determine the potential for cost savings with widespread implementation of the rule.

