#### Economic evaluation

We will adopt a decision analytic approach, whereby we will identify the incremental cost savings from both a health care sector and a societal perspective of the active strategy of implementation [55]. The model will consider two hypothetical cohorts of patients, a "usual practice" cohort, and a cohort where practice is as dictated through the active dissemination of the decision rule. Results will be generated through probabilistic analysis, as this is superior to simple deterministic analysis [56,57]. The principal resources in this analysis will be the costs of radiography and the associated patient time costs. In addition, the costs of settlement of litigation, the incremental costs of follow-up treatment due to missed fractures, and the costs of neurological deficits will be included. The design of the decision analytic model, sources of data, and analysis of uncertainty are provided in a supplemental file [58-64] [see Additional file 1].

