### Sample size

#### Required patients

Refer to the supplemental file for more details on the sample size calculation [45,65-67] [see Additional file 2]. The study is based on a complex, stratified, matched-pair cluster design, such as a stratification factor type of hospital (teaching vs. community), a matched-pair (hospitals matched according to baseline cervical spine radiography), and cluster randomization (unit of randomization is the hospital and unit of analysis is the patient) [45,68]. Let k be the number of pairs needed to achieve power100(1-β)% for detecting a difference Δ in the cervical spine radiography event rates at the two-sided 100(1-α)% significance level. From the phase II study, the cervical spine radiography event rates for non-transfer patients at the participating sites ranged from 63.3% to 85.9%, with an average of 76% and an annual accrual per hospital of approximately 400 patients. We estimate that the between-cluster variance component is 0.00636, based on Gail et al (1992) for the COMMIT trial (i.e. *Var*(*d*_*j*_) = 0.0066125) [66]. It is expected that the event rate in the control group will not change. Based on a consensus of the participating site investigators, we believe that for the intervention group, a 15% relative decrease (or an absolute decrease of 11.4% from the baseline rate of 76%) in the event rate would be considered a minimal clinically important change (i.e. Δ = 0.114). Then for a significance level of 0.05 and power of 80%, *k *=(1.96+0.84)^2^(0.0066125)/.114^2 ^= 3.9891 and the number of matched-pairs required is (7/5)(3.9891) = 5.5847 where 7/5 adjusts for the small number of degrees of freedom [65]. Thus, six matched-pair clusters will be required with 400 patients per hospital for each of the ''before'' and ''after'' periods in the primary analysis. Because the exact benefits of stratifying by teaching and community hospitals in this matched-pair design are difficult to quantify, a conservative approach is adopted and the six matched-pair clusters will be selected [67]. Furthermore, we estimate that the sample size for the ''decay'' period will be the same as for the ''after'' period, and that this will allow sufficient power in the secondary analysis to identify complete decay of effect from the ''after'' to the ''decay'' period. In addition, this will provide a sufficient sample to calculate a precise estimate of the decay rate.

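### The primary outcome is worded as plain films only and no outcome counts CT, so a patient sent straight to CT would score the same as one cleared clinically

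*Protocol article*

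**What the plan says.** The only specific definition of the primary outcome is under Outcome measures and data collection, Measures of clinical impact: "the proportion of eligible blunt trauma patients referred for plain cervical spine radiography during the initial ED visit". Elsewhere the wording is looser. Specific objectives has "proportion of potential injury patients referred for radiography; this is the primary study objective", the ascertainment sentence reads "Radiology reports and census lists will be used to determine if cervical spine radiography was performed", and the outcome list under Data analysis also refers to radiography without naming a modality.

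CT is named once, in the description of the phase II validation study, where injury was assessed by "standard plain radiography of the cervical spine, optional flexion-extension views, and CT, if clinically indicated". It appears there as an item distinct from plain radiography. For phase III, CT is not mentioned in any clinical impact outcome, in the requisition process or in the economic measures printed in the article.

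Two further passages depend on the same term. At intervention sites, "All cervical spine radiography ordered in the ED will require that the ordering physician complete a special paper or computer-based requisition", with an override allowed if a reason is given. Missed-injury surveillance monitors logs to "identify return visits by patients who do not undergo radiography during their ED visit".

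**The concern.** The rule governs whether a patient needs imaging or can be cleared clinically, and the benefits claimed for it are fewer unnecessary images, less immobilisation, faster flow and lower cost. An outcome that measures this decision has to separate imaged from un-imaged patients. The definition given separates patients with a plain film from everyone else, so a CT-only patient falls among those who count as a success for the rule.

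This matters most if the shift to CT differs by arm. The checklist exists only at intervention sites. If it covers plain films but not CT, those sites have an unchecked route to imaging during the after and decay periods that has no counterpart at control sites. Matching and change from baseline cannot remove a shift that the intervention itself causes. The surveillance group is also left unclear, because a CT-only patient may or may not be someone who did not undergo radiography.

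**Working it through.** **Step 1. The plan's own figure.** Inputs from Sample size, Required patients: baseline rate 0.76; relative reduction 15%, so Δ = 0.15 × 0.76 = 0.114; Var(d) = 0.0066125; the calculation is "for a significance level of 0.05 and power of 80" percent, two-sided.

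k = (1.96 + 0.84)² × 0.0066125 / 0.114² = 3.9891, and 3.9891 × 7/5 = 5.5847, so 6 pairs. Then 12 sites × 400 = 4,800 patients per period. This reproduces the plan and is not in dispute. The power of the planned paired t-test with 6 pairs (5 df, non-central t) at Δ = 0.114 is 78.2%.

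**Step 2. What the definition does.** Divide eligible patients at a site into P (plain film, with or without CT), C (CT only) and N (no imaging), with P + C + N = 1. The outcome as worded is P. The quantity that answers the trial's question is P + C = 1 − N. For each pair, taking the intervention-minus-control difference in change from baseline:

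difference in P = difference in (P + C) − difference in C.

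- A patient who has a plain film and then CT is in P and is counted correctly.
- If C rises equally in both arms, its difference is zero and the primary contrast is unaffected.
- If C rises by s more at intervention sites, P falls by s with no change in imaging.

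**Step 3. Size over an assumed range.** The article gives no CT-only rate, so s from 0 to 11.4 points is an assumption; the upper end is simply the value that would mimic the whole target. The last column assumes no true change in imaging, the same shift in every pair and the plan's Var(d), so the non-centrality is s / √(0.0066125/6) = s / 0.0332.

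| s (points) | Patients per 400 | Share of 11.4 | Fall in all imaging if plain films fall 11.4 points | Chance of p < 0.05 on plain films if imaging does not fall |
|---|---|---|---|---|
| 0 | 0 | 0% | 11.4 (15.0% relative) | 5% |
| 2 | 8 | 18% | 9.4 (12.4%) | 8% |
| 3 | 12 | 26% | 8.4 (11.1%) | 12% |
| 5 | 20 | 44% | 6.4 (8.4%) | 23% |
| 8 | 32 | 70% | 3.4 (4.5%) | 49% |
| 11.4 | 45.6 | 100% | 0 | 78% |

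**The case against.** The strongest reply is that the text is loose rather than fixed. The word *plain* appears once in the outcome description, after *such as*, while the objective, the ascertainment sentence and the analysis list say only radiography. An all-imaging outcome may have been intended. That is fair, but it supports correcting the text: the one specific definition leaves CT out, and nothing elsewhere brings it in.

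Several stronger readings are tempting and are not supported.

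- *The checklist pushes physicians to CT.* The article does not say whether CT requests are exempt from the requisition. A physician who wants a film can override on the same form by giving a reason. The mechanism is possible, not shown.
- *General growth in CT use over three years biases the result.* Concurrent randomised controls and pair differences in change from baseline largely cancel a common drift. It could still affect a before–after reading of a single site.
- *Any incentive is confined to the after period.* Under Design, the implementation strategies continue through the decay period.
- *Phase II shows that CT-only work-up was already in use.* The phase II text lists plain radiography as the standard test, with CT if indicated. It reports no CT-only patients.

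Length of stay, analysed in the same way, might hint at wholesale substitution because imaged patients would not leave sooner. It cannot identify or measure it. On costs, the article says "The principal resources in this analysis will be the costs of radiography and the associated patient time costs", but the design of the model is in a supplementary file that is not shown, so no criticism of the model is made here.

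**Conclusion.** The point holds as a weakness in the definition of the primary outcome. As worded, CT-only patients are non-events, the sections do not agree on modality, and no phase III outcome would reveal a switch. The possible error is exactly one point of spurious effect per point of differential film-to-CT shift, against a target of 11.4 points.

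How large that shift would be cannot be learned from the article. A reader might infer that the trial is biased towards the intervention; the documents do not support this, since they give no CT-only rate and no evidence of substitution. The bias also requires that CT orders escape the requisition and that the shift exceeds the one at control sites. The point should be fixed, with moderate confidence, because the repair is cheap and removes an alternative explanation for a positive result.

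**What to change.** Define the primary outcome as the proportion of eligible patients referred for any cervical spine imaging, plain film or CT, at the initial ED visit. Use that wording in Specific objectives, in the outcome section and in the list of analysis variables. Report plain-film and CT-only proportions by arm and period as secondary outcomes. Apply the same definition when identifying un-imaged patients for missed-injury surveillance, and state whether CT requests pass through the special requisition.

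The cost is one more field taken from radiology reports that study staff already review, plus the change of wording. The downside is that the observed reduction may be smaller than for plain films alone. It is best settled before abstraction starts: a later change could mean returning to as many as 14,400 records and redefining the primary outcome with results in view.

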For each of the following clinical impact outcome variables, the change from the "before" to "after" periods in the proportions (or means) for each cluster will be determined, used in the calculation of the differences in the event rates (mean response) for each intervention and control site pair, and analyzed according to the above analysis plan. Clinical impact outcome variables include: cervical spine radiography ordering proportions, proportion of missed fractures, proportion of serious adverse outcomes, length of stay in ED in minutes and, patient satisfaction with the proportions indicating "very satisfied" or "satisfied."

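### The 30-day return-visit search for missed injuries covers only patients not X-rayed, a share the intervention is meant to change, so one rule at every site does not guarantee equal ascertainment between arms

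*Protocol article*

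**What the plan says.** Under Outcome measures and data collection (Measures of clinical impact), the missed-injury outcome is the "number of clinically important CSI not identified during initial ED visit". That definition does not depend on whether the patient was X-rayed. Three routes of detection are then described:

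- **ED return visits.** Logs are "monitored for 30 days to identify return visits by patients who do not undergo radiography during their ED visit".
- **Radiology quality assurance.** "The more common missed fracture cases due to mis-reading of the radiograph will be identified through the normal radiology department quality assurance processes."
- **Neurosurgery logs.** "we will review the neurosurgery patient logs at all neurosurgical centers that are the traditional referral sites for the study hospitals." No restriction by radiography status is stated.

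The section concludes: "Application of the same surveillance approach, regardless of phase or intervention group, minimizes the likelihood of bias."

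For serious adverse outcomes, such as a neurological deficit that develops after ED assessment, the protocol says: "We will use the same surveillance approach described above for identifying missed fractures."

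Under Data analysis, the before-to-after changes compared within site pairs include "cervical spine radiography ordering proportions, proportion of missed fractures, proportion of serious adverse outcomes". Under Sample size, radiography is expected to stay at 76% in the control group and to fall by 15% relative, or 11.4 points, in the intervention group.

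**The concern.** Whether a patient's return visits are searched depends on whether radiography was done at the first visit. That is the behaviour the trial sets out to change. A rule worded identically for every site therefore applies to different fractions of patients in the two arms once the intervention starts.

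Taking before-to-after changes removes stable differences between hospitals, such as better or worse local quality assurance. It does not remove a shift in the mix of search routes that is planned for the intervention sites only.

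At stake is the comparison of the combined missed-injury count and of serious adverse outcomes. Safety is part of the stated goal under Specific objectives, and these are the outcomes that speak to it. Late deficits are the clearest case. Re-reading a film is aimed at an injury that was visible and overlooked, not at a deficit that appears later. For that outcome an X-rayed patient discharged from the ED is left mainly with the neurosurgery logs, while a patient not X-rayed also has the return-visit search.

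**Working it through.** **Inputs from the protocol.** Baseline radiography rate 76%, no change expected in controls, 15% relative decrease in the intervention group, about 400 patients per hospital per period (Sample size). With six hospitals per arm this is 6 × 400 = 2,400 patients per arm per period. A relative reduction of 25% to 50% is thought achievable (Potential benefits).

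**The plan's own figures.** 0.15 × 0.76 = 0.114, so the planned intervention rate is 0.76 − 0.114 = 0.646. The number of pairs also reproduces: (1.96 + 0.84)² × 0.0066125 / 0.114² = 3.9891; × 7/5 = 5.5847, rounded up to 6. The protocol gives no figure for the ascertainment of missed injuries.

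**Share under the return-visit search** = 1 − radiography rate, 'after' period:

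| Scenario | Radiography rate | Share searched | Of 2,400 |
|---|---|---|---|
| Control | 76% | 24.0% | 576 |
| Intervention, design effect | 64.6% | 35.4% | about 850 |
| Intervention, 25% relative reduction | 57% | 43% | 1,032 |
| Intervention, 50% relative reduction | 38% | 62% | 1,488 |

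At the design effect the ratio is 0.354 / 0.240 = 1.475, or about 274 more patients searched.

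**What this could do to detection.** Let sR be the probability of detecting a missed injury in a patient not X-rayed, and sQ the same for an X-rayed patient. Neither is in the protocol; both are assumptions. Assume also that the true risk of a miss is the same in the two groups, which the protocol does not say either. Neurosurgery logs are left out at first.

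Overall detection = (1 − p) × sR + p × sQ, where p is the radiography rate.

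| sR | sQ | Control | Intervention | Ratio |
|---|---|---|---|---|
| 0.9 | 0.3 | 0.444 | 0.512 | 1.15 |
| 0.9 | 0.5 | 0.596 | 0.642 | 1.08 |
| 0.7 | 0.7 | 0.700 | 0.700 | 1.00 |
| 0.5 | 0.9 | 0.804 | 0.758 | 0.94 |

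The difference between arms is 0.114 × (sR − sQ). It is zero only if the two routes detect equally well, and its sign follows whichever route is better.

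**Adding neurosurgery logs.** Suppose, again as an assumption, that these logs independently find half of the misses in both groups. For sR = 0.9 and sQ = 0.5 the combined probabilities are 1 − 0.1 × 0.5 = 0.95 and 1 − 0.5 × 0.5 = 0.75. Control: 0.24 × 0.95 + 0.76 × 0.75 = 0.798. Intervention: 0.354 × 0.95 + 0.646 × 0.75 = 0.821. The ratio falls from 1.08 to about 1.03.

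**How many cases.** Taking 0.9% fractures (Abstract) to 2.0% important injuries (phase II results), 2,400 patients give 21.6 to 48 injuries per arm. If 10% were missed (an assumption), that is about 2 to 5 per arm. At the widest gap in the table (0.512 − 0.444 = 0.068), the expected difference in detected cases is at most 0.068 × 4.8 = 0.33.

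**The case against.** The strongest reply is that the return-visit search has a narrower target, namely fractures missed because no film was ordered. Only patients not X-rayed can have that event, and all of them are searched in both arms. For that target, 24.0% versus 35.4% is simply the population at risk. This stands, and it is also the harm that the intervention could most plausibly increase. It does not cover the outcome as defined, which includes misses in X-rayed patients, nor late deficits in X-rayed patients. Both enter the between-arm comparison.

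A reader might infer that X-rayed patients depend on quality assurance alone. The text does not support that. Neurosurgery logs have no stated limit by radiography status, and study staff review daily logs, ED records, radiology reports and inpatient records at all sites and in all periods.

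A reader might also infer that the uniformity sentence is false. As a statement of the rule it is true: the procedure is the same in every phase and group. What does not follow is that equal procedure yields equal detection.

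Finally, a reader might infer that intervention sites will show a spurious excess, for example 8% with assumed detection of 90% against 50%, or 22% with 90% against 20%. These values are not from the protocol, they assume equal miss risks, and they leave out the neurosurgery logs. Reversing the assumption (50% against 90%) gives 0.94, so even the direction is open. Nor does the protocol say that the safety board would act on between-arm ratios of these counts; its mandate concerns adverse patient outcomes generally.

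**Conclusion.** The concern holds in a limited form. One of the routes for finding missed injuries and late adverse outcomes is tied to index radiography, which the intervention is planned to change. A common rule therefore does not ensure equal ascertainment of the combined missed-injury count or of serious adverse outcomes.

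The planned difference in coverage, 24.0% against 35.4%, follows directly from the protocol's own rates. The resulting bias does not: with assumed detection probabilities and equal miss risks, the ratio of detection lies at about 0.94 to 1.15 before neurosurgery logs are counted, and closer to 1 after. Its size and direction are unknown. Expected counts are small, so the distortion is probably a fraction of a case per arm, although with so few events one unevenly found case would be visible. The primary outcome is not affected. This is an inexpensive improvement, not a flaw that undermines the trial.

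**What to change.** - Match the 30-day ED return-visit logs against every eligible patient, imaged or not, at all 12 sites and in all three periods.
- Keep the neurosurgery-log review, and state explicitly that it applies to all eligible patients.
- Base the between-arm comparisons of missed injuries and of serious adverse outcomes on these common sources.
- Report misreads found through radiology quality assurance separately.

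Coverage by the return-visit search then becomes 100% in each arm (2,400 patients per period) and no longer depends on radiography. The cost is some added clerical time for log matching. No telephone follow-up is needed, which is the expense the protocol set out to avoid.
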